### Quality Control Procedures

All study personnel involved in specimen collection, handling, processing and testing will undergo training and regular supervision. The surveillance project includes detailed laboratory procedures manuals outlining standard procedures. Regardless of laboratory where testing was done, all positive and a representative sample of 10% of negative specimens will be retested to ensure validity of test procedures. Internal and external quality control.

### Clinical Specimen Collection Flow

Samples tested on site with results provided same day:

- HIV Determine and Uni-gold with finger prick whole blood
- SD Bioline Syphilis 3.0 rapid syphilis test with finger prick whole blood
- Determine HBsAg Hepatitis B rapid testing with finger prick whole blood

Samples collected at venues for processing at study laboratory:

- Venous blood sample for syphilis confirmatory testing with RPR or VDRL and viral load testing using Xpert Viral Load Assay (patients with positive rapid test results for syphilis and HIV, respectively)

- Whole blood may be held at 2-8 °C for up to 72 hours, prior to preparing and testing the specimen.
- Dried blood spots for posterior HIV and STI testing through PCR will be stored at ambient temperature with desiccant bags or in low temperature freezer based on availability
- 20 ml urine for *Neisseria gonorrhoeae*, *Chlamydia trachomatis* and the first 100 samples for *Trichomonas vaginalis* (men meeting key population definitions) stored at ambient temperature for up to 24 hours.
- Rectal swabs for men and transgender women meeting key population definitions 
- Vaginal swabs for *Neisseria gonorrhoeae*, *Chlamydia trachomatis* and *Trichomonas vaginalis* from women meeting key population definition
- Samples tested at study Laboratory will provide results to participants within 2 weeks of receipt using the participant ID number 
  - RPR or VDRL for confirmation of syphilis
  - *Neisseria gonorrhoeae* (vaginal, urine or anal, as applicable)
  - *Chlamydia trachomatis* (vaginal, urine or anal, as applicable)
  - *Trichomonas vaginalis* (vaginal or urine, as applicable)
  - HIV viral load 

Quality control for HIV testing will be conducted for all positives and 10% of negatives

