## II. SUMMARY

**Purpose:** Sex workers, men who have sex with men (MSM) and transgender women bear a disproportionate burden of HIV in Angola. This programmatic mapping study in Angola aims to identify and map priority prevention areas (PPAs) —also known as high transmission areas or “hot spots” in the district where HIV prevention activities are needed; to characterize and map high risk venues and events in these PPAs; and to describe characteristics of sex workers, MSM and transgender women socializing or working at these venues. We will also estimate the prevalence of HIV, syphilis, gonorrhea, chlamydia and trichomoniasis for these groups in the PPAs. The study will use dried blood spot or whole blood collection to assess viral load suppression in HIV-infected patients who are receiving antiretroviral therapy (ART).

**Participants:** In each geographic area of data collection, participants will include community informants, site representatives who are knowledgeable about the sites, and venue patrons and workers which will include sex workers, MSM and transgender women. Respondent driven sampling (RDS) may be used to recruit MSM, transgender women or sex workers.

**Procedures:** Interviewers ask community informants for names and locations of venues where people meet new sexual partners. Next, a representative at each venue is interviewed to learn about activities at the venue. Finally, interviews, HIV, STI and CD4 testing are conducted with workers and persons socializing at venues, as well as a separate sample of MSM and transgender women, to learn about their sexual behavior, HIV risk, and exposure to prevention programs, as well as their HIV status. Finger prick blood samples will be collected for rapid HIV, syphilis and Hepatitis B diagnosis. Additional finger prick blood and venous blood samples will be collected among HIV positive participants to obtain CD4 T-cell count and plasma HIV-1 RNA level. Vaginal and anal swab specimens for women and urine and anal swab specimens from men will be collected for subsequent gonorrhea, chlamydia and trichomoniasis testing.

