- To characterize and map high risk venues and events in each PPA where key populations meet new sexual partners.
- To characterize the men and women who visit high risk venues and events and women who work at these venues and identify gaps in HIV prevention services (HIV Testing and Counseling (HTC), condoms, and syndromic/etiologic STI management).
- To characterize key populations: sex workers, men who have sex with men and transgender women that visit venues in Luanda.
  - To estimate the prevalence of HIV, the percent of key populations with early HIV infection, among people with HIV the percent who is eligible for ART, and the percent virally suppressed.
  - To estimate the percent of people at each stage of the HIV continuum of care between HIV diagnosis and viral suppression.
  - To estimate the prevalence of syphilis, Hepatitis B, gonorrhoea, chlamydia and trichomoniasis
- To inform stakeholders about high-risk areas for HIV transmission
- To facilitate provincial action plans for HIV prevention among key populations

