#### ***Step 4: Key population interviews among site workers and patrons; HIV, CD4 and STI testing Selection of Sites and Events for Worker and Patron Surveys and Testing***

Individual interviews and HIV testing with male and sex workers, men who have sex with men and transgender women will be performed in a sample of sites and events visited in the previous step. Social mobilizers will assist interviewers in identifying sex workers, men who have sex with men and transgender women at venues. At venues where social mobilizers accompany interview teams, all people identified by social mobilizers as potentially people from key populations will be interviewed. Additionally, people at venues will be approached randomly by interviewers and will not be screened for eligibility based on history of sex worker or same-sex practices. Through random selection, some participants may not be sex workers, MSM or transgender people.

Sites will be selected using a systematic fixed-interval sampling strategy with the probability of selection proportional to the size of the site. The size of a site is defined by the number of people socializing at the venue during a busy time as reported by the site informant. A sampling frame of sites that were confirmed to exist and be in operation and those that were temporarily closed during site visits (Step 3) will be constructed, with sites and events sorted by province/geographic area, type and size. Prior to interval selection, venues eligible for individual interviews are sorted by geographic location, as indicated by geographic code, and size of venue.

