|-------------------------|------------------------------------------------------------------------------------------------------------------|--------------------------|-------------------------------------------------------------|
| Whole Blood             | Determine and Unigold HIV rapid tests                                                                            | Study venue              | Finger prick                                                |
| Whole Blood             | CD4 count, PIMA Analyzer                                                                                         | Study venue              | Finger prick                                                |
| Whole Blood             | Dried Blood Spots for future analysis                                                                            | Study venue              | Finger prick                                                |
| Whole Blood             | Determine TP rapid syphilis test                                                                                 | Study venue              | Finger prick                                                |
| Whole Blood             | Determine HBsAg rapid Hepatitis B test                                                                           | Study venue              | Finger prick                                                |
| Serum                   | RPR or VDRL for syphilis                                                                                         | Study Laboratory, Luanda | 10 ml whole blood in EDTA, EDTA-PPT, or ACD collection tube |
| Serum                   | Xpert Viral load test                                                                                            | Study Laboratory, Luanda |                                                             |
| Vaginal swab from women | Xpert CT/NG ( C. trachomatis / N. gonorrhoeae )
Xpert TV ( Trichomonas vaginalis )       | Study Laboratory, Luanda | Swab                                                        |
| Urine from men          | Xpert CT/NG ( C. trachomatis / N. gonorrhoeae )
Xpert TV ( Trichomonas vaginalis ) n=100 | Study Laboratory, Luanda | 20 ml                                                       |

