### **E. Sample Size**

The sample size will be calculated based on the budget and the estimated number of sex workers, men who have sex with men and transgender women that are thought to be reachable (Table 3). For PLACE/Programmatic mapping the exact number of each population interviewed will depend on the site identification, verification and patron and worker interview steps.

Approximately 2000 men and women will be interviewed and tested for HIV at venues in Luanda. We expect to recruit approximately 600 sex workers, 600 men who have sex with men and 200 transgender women. Around 600 participants could be from the general population. Approximately 400 female sex workers will be recruited in Cabinda using RDS.

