**Table 3 Summary of interviews to be completed by province**

| Population                                      | Luanda | Benguela | Bié | Cunene | Cabinda | Total |
|-------------------------------------------------|--------|----------|-----|--------|---------|-------|
| Community informant interviews                  | 500    | 500      | 500 | 500    | 0       | 2000  |
| Venue informant interviews                      | 700†   | 500      | 500 | 500    | 0       | 1500  |
| Behavioral interview and HIV/STI testing |        |          |     |        |         |       |
| Female sex workers                              | 600    | 400      | 400 | 400    | 400     | 2200  |
| Men who have sex with men                       | 600    | 400      | 400 | 400    | 0       | 1800  |
| Transgender women                               | 200*   | ‡        | ‡   | ‡      | 0       | 200*  |
| Other men and women at venues                   | ‡      | ‡        | ‡   | ‡      | 0       | ‡     |

\* Could be less based on the number and percent of people at venues who identify as transgender, has received money for sex and who are men who have had sex with a man in past 12 months. † If there are more than 700 venues are identified in Luanda, a sample of venues will be selected. \*\*The sample must be confirmed by UNC staff prior to field work. \*\* ‡ No defined sample size as sample will depend on distribution of key populations in venues sampled.

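### Male trichomoniasis is tested only in the first 100 urine samples, so the estimate would describe early recruits rather than the male and transgender key populations

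*Protocol*

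**What the plan says.** In the Protocol, Clinical Specimen Collection Flow, male urine is tested for gonorrhoea and chlamydia without a limit, but for trichomoniasis only up to a fixed count: "Chlamydia trachomatis* and the first 100 samples for *Trichomonas vaginalis* (men meeting key population definitions"). Table 2 (Specimens and laboratory tests) repeats the limit in the row for urine from men: "Xpert TV ( Trichomonas vaginalis ) n=100". The vaginal-swab row for women carries no limit.

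The estimate these tests serve is stated twice. Section II (Summary) says: "We will also estimate the prevalence of HIV, syphilis, gonorrhea, chlamydia and trichomoniasis for these groups in the PPAs". Section V (Objectives), under key populations visiting venues in Luanda, lists: "To estimate the prevalence of syphilis, Hepatitis B, gonorrhoea, chlamydia and trichomoniasis". Section VIII.B (PLACE Analysis) says that weights will be built to give unbiased population-based estimates.

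Section VI.E gives the planned numbers for Luanda: "We expect to recruit approximately 600 sex workers, 600 men who have sex with men and 200 transgender women". Table 1 also shows urine collected from male sex workers, for whom no separate number is given.

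Two other places, the STI-testing paragraphs of Step 4 and the section on risk assessment and collection of biologic specimens, offer trichomoniasis testing to participants who meet the key-population criteria and mention no limit.

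**The concern.** Taking the first 100 samples selects by order of collection. Once the 100th urine is tested, nobody enrolled later can contribute a result, whatever their venue or group.

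Early and late recruits need not be alike. Step 4 says that key-population participants will be asked about further venues and that the venue list will grow until the targets are met. People at venues added this way tend to come late, and those reached after the limit drop out of this one estimate. The 100 tests also pool men who have sex with men, male sex workers and transgender women, and the rule leaves that mix to chance.

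At stake is one prevalence estimate, trichomoniasis in male and transgender key populations. Gonorrhoea, chlamydia and the estimate for women are untouched.

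**Working it through.** **Inputs**
- Tests: 100 (Clinical Specimen Collection Flow; Table 2). The protocol gives no formula, precision target or assumed prevalence for this figure, so it cannot be reproduced.
- Planned in Luanda (Section VI.E): 600 + 200 = 800. Male sex workers come on top, number not stated.
- Four mapping provinces (Table 3): "Men who have sex with men | 600 | 400 | 400 | 400 | 0 | 1800". The sum 600 + 400 + 400 + 400 = 1,800 reproduces the printed total. Adding 200 transgender women gives 2,000.
- Men tested per venue and within-venue correlation: not in the protocol. Assumed here as 2 to 10 men and 0.05 to 0.10.

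**Coverage.** 100 / 800 = 12.5% could have a result, and 800 − 100 = 700 could not. This reads the limit as covering transgender women, because the specimen-collection section groups them with men for urine.

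**Venues reached before the limit**, at m eligible participants per venue:

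| m | first 100 (100/m) | all 800 (800/m) |
|---|---|---|
| 2 | 50 | 400 |
| 5 | 20 | 160 |
| 10 | 10 | 80 |

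**Weights.** A survey weight is the inverse of the selection probability. For anyone after the 100th urine that probability is zero and the inverse does not exist.

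**Bias.** Let f be the share tested, and p_E and p_L the prevalence in early and later recruits. Relative to all those enrolled, bias = p_E − [f·p_E + (1 − f)·p_L] = (1 − f)(p_E − p_L). With f = 0.125 the factor is 0.875.
- Illustration, early 2% and later 6%: true value 0.125 × 2 + 0.875 × 6 = 5.5%, bias −3.5 points.
- Reversed, early 6% and later 2%: true value 0.125 × 6 + 0.875 × 2 = 2.5%, bias +3.5 points.
- Equal prevalence: bias zero.

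**Clustering (illustrative).** Design effect = 1 + (m − 1) × correlation.
- m = 2: 1.05 to 1.10, so the effective number is 100/1.05 = 95 to 100/1.10 = 91.
- m = 10: 1.45 to 1.90, so the effective number is 100/1.45 = 69 to 100/1.90 = 53.

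**Interval for a systematic sample.** k = expected eligible urines / 100. With 800 expected, k = 8. If testing ran over 2,000 people, k = 8 would give 2,000 / 8 = 250 tests, so k has to be matched to the scope.

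**The case against.** A reader might infer that the first 100 samples come from a few neighbouring venues in the first area visited, since Step 4 says that "venues eligible for individual interviews are sorted by geographic location, as indicated by geographic code, and size of venue". The protocol does not support that. The sort is done before interval selection and orders the sampling frame, which helps to spread a systematic sample over areas. It is not a visit schedule, the order of visits is not stated, and several teams could work in parallel. What stands is only that later recruits are excluded, whatever the order.

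Nor does the protocol support a complaint that the estimate fails for the other provinces, because Section V ties this objective to venues in Luanda.

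It is also fair to say that the full key-population sample is not a clean probability sample. Everyone whom social mobilizers identify is interviewed, and the venue list expands until targets are met. A systematic subsample therefore represents the enrolled men and transgender women, and the wider population only as well as the main sample does. That limits the gain but does not justify adding a second, avoidable selection.

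The stakes are modest: Table 4 has no trichomoniasis indicator. Precision is not the argument either. Two positives in 100 give an exact 95% interval of 0.2% to 7.0% before clustering, and a fix that keeps 100 tests leaves that interval unchanged. The clustering loss depends on venue size, and Step 4 expects most venues to be small.

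**Conclusion.** The point holds in limited form. The protocol fixes a first-come rule for a result that it intends to report as a population prevalence. Nothing in it spreads the 100 tests over fieldwork or calls them a pilot. About 700 of the 800 men who have sex with men and transgender women planned in Luanda would have no chance of a result. That count rests on planned numbers: Section VI.E and the notes to Table 3 say they may change, and male sex workers are not in it.

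The bias may be zero, and its sign is unknown. It is 0.875 times the difference in prevalence between early and later recruits, which the protocol gives no means to estimate. The effective numbers of 91 to 95 (2 men per venue) and 53 to 69 (10 men per venue) illustrate assumed values and are not findings about this study. The change is worth making because it removes a selection at almost no cost.

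**What to change.** 1. Reconcile the uncapped offers of trichomoniasis testing (Step 4; risk assessment and collection of biologic specimens) with the limit of 100 (Table 2; Clinical Specimen Collection Flow), so that the number of urines to be tested is settled first.
2. If a limit of about 100 remains, replace the first-100 rule with a systematic sample over all Luanda fieldwork: every k-th eligible urine from men who have sex with men, male sex workers and transgender women, in specimen-ID order, from a random start.
3. Set k before Step 4, once site verification has given an expected number of eligible urines: k = expected number / 100, about 8 if 800 are expected. It has to be set in advance, because urine is held at ambient temperature for up to 24 hours and leftovers are stored only with consent.
4. If k changes during fieldwork, include the subsampling fraction in the weight. A constant k cancels out of the prevalence.
5. If the first-100 rule is kept, report the result as descriptive of the early samples, not as a population prevalence.

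The cost is small: the laboratory flags each k-th specimen and the planned number of tests stays about the same. The downside is that the final number will vary around 100 with actual enrolment. At k = 8, for example, 600 urines would give 75 tests.

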### **Test results**

As noted earlier, rapid HIV test results will be returned to participants by a trained counselor after the necessary pre- and post-test counseling. Negative results will be provided 30 minutes after testing. Participants with positive results will receive a preliminary positive results 30 minutes after being tested and the confirmatory results in 2 weeks. HIV-positive participants will be referred to HIV treatment sites for evaluation and therapy if needed.

If found to be HIV-positive, participants will be encouraged to refer all partners for HIV testing at a predetermined local clinic or VCT site, and the HIV-positive participant will be referred to a site where they will be able to access free treatment. However, such partners and their test results will not be a part of this survey and will not be linked in any fashion with the HIV-infected subjects in this survey. There will not be a separate effort by study clinic staff participating in this survey to try to contact (telephonically or personally) any partners of any subjects in this survey (regardless of test results) since this would constitute a clear violation of the confidentiality agreement by the survey's PI with the subject. The subject will be given the option for him/her to contact his/her sexual partners for follow-up.

Participants with signs and symptoms of STI will be referred for treatment at a local health center. Participants will be provided as many partner notification slips as requested and will be encouraged to refer their partners to a pre-determined local clinic for free treatment.

Participants will receive a test results card with their survey number and the place and date to collect other test results. This card should be presented at the study laboratory to collect STI and viral load results. Results for tests processed at the study laboratory, such as *N. gonorrhoeae* and *C. trachomatis* and viral load testing will be available in 2 weeks. Participants with positive test results will be referred for treatment.

If a participant loses their results card and the only link to their laboratory tests is a unique identifier code, it will be used to return STI and viral load test results. During specimen collection, participants will be assigned a unique identifier code based on personal information such as birth year, first letters of their parents' names and gender. This unique identifier will not permit study staff to identify the participant. It will be recorded with the specimen roster in case the participant returns to collect results without their results card. If a participant comes to the laboratory without their results card, laboratory staff will ask the participant a series of questions to reconstruct the unique identifier code, look up the results and return the test results to the participant.

### ***Indications for antiretroviral therapy (ART)***

HIV-positive patients, confirmed by two rapid tests and a CD4 test, will be referred to ART programs in clinical sites managed by the Angolan government. A referral letter will be prepared with the participant's name, demographics and results of HIV, CD4 and viral load tests. This letter will be provided to the patient in a closed envelope and will not be linked to any survey materials. HIV-positive patients will be provided with information on the closest ART site and attendance times. At the ART site, patients will receive a clinical evaluation and ART will be initiated according to these findings.

The government of Angola has a treatment program for HIV-positive patients. There is at least one treatment site in each of the cities where the survey will take place. Although the point of entry for highly active antiretroviral therapy (HAART) in Angola is a CD4 count < 350 or a clinical diagnosis for AIDS, people are evaluated and also provided counseling on healthy living (e.g., safe water, food, information about hygiene and activities to avoid), given counseling to avoid transmission to sex partners or unborn children, evaluated for tuberculosis, and where indicated provided prophylactic antibiotics against opportunistic infections.

